# Study protocol for the DISTINCT trial: inDividual, targeted thrombosIS prophylaxis versus the standard ‘one-size-fits-all’ approach in patients undergoing Total hIp or total kNee replaCemenT – a national, multicentre, randomised, multiarm, open-label trial

**DOI:** 10.1136/bmjopen-2025-101180

**Published:** 2025-10-06

**Keywords:** Orthopedics, Thromboembolism, Hip, Knee

## Abstract

**Introduction:**

Patients undergoing total hip arthroplasty (THA) and total knee arthroplasty (TKA) are considered to have a symptomatic venous thromboembolism (VTE) risk of 1.0%–1.5% despite thromboprophylaxis. Fast-track treatment protocols have substantially lowered the VTE risk in most patients. Hence, the majority of patients may be unnecessarily exposed to the burden and risk of thromboprophylaxis. On the contrary, there are still patients with a high VTE risk who develop VTE despite thromboprophylaxis. Thus, tailored thromboprophylaxis treatment may potentially reduce both VTE and bleeding risk.

**Methods and analysis:**

The DISTINCT (inDividual, targeted thrombosIS prophylaxis versus the standard ‘one-size-fits-all’ approach in patients undergoing Total hIp or total kNee replaCemenT) trial is a national, multicentre, randomised, multiarm, open-label trial. The main objective is to study whether tailored thromboprophylaxis reduces the occurrence of symptomatic VTE (primary outcome) and major bleeding (primary safety outcome) within 90 days after THA/TKA in comparison with standard thromboprophylaxis. Patients with a low, intermediate or high predicted VTE risk (based on the Thrombosis Risk Prediction following total hip and knee arthroplasty score (TRiP(plasty) score)) will be included in the DISTINCT-1, DISTINCT-2 or DISTINCT-3 studies, respectively. In the DISTINCT-1 trial, 3478 patients will be randomly allocated to receive either in-hospital thromboprophylaxis or standard prophylaxis. In the DISTINCT-2 cohort study, 2500 patients will receive standard prophylaxis. In the DISTINCT-3 trial, 4100 patients will be randomly allocated to receive either 6 weeks of high-dose thromboprophylaxis or standard prophylaxis. Standard prophylaxis consists of a low dose of any approved thromboprophylactic agent for 4 weeks. We hypothesise that (1) the efficacy of in-hospital only thromboprophylaxis is non-inferior in preventing VTE and equally safe compared with standard prophylaxis in patients with a low VTE risk (DISTINCT-1) and (2) prolonged high-dose thromboprophylaxis is superior in preventing VTE as compared with standard prophylaxis in patients with a high VTE risk (DISTINCT-3). Patients with intermediate VTE risk will be observed to evaluate VTE and bleeding rates (DISTINCT-2).

**Ethics and dissemination:**

The protocol has been approved by the Medical Research Ethics Committee Leiden-Den Haag-Delft, EU-trial-number 2023-510186-98. Study results will be disseminated through peer-reviewed journals and during international conferences.

**Trial registration number:**

NCT06581965.

STRENGTHS AND LIMITATIONS OF THIS STUDYThe DISTINCT (inDividual, targeted thrombosIS prophylaxis versus the standard ‘one-size-fits-all’ approach in patients undergoing Total hIp or total kNee replaCemenT) trial is designed as a pragmatic trial to be integrated into routine clinical practice, allowing for the determination of an individual’s thromboprophylaxis regimen prior to surgery.The DISTINCT trial is the first thromboprophylaxis trial following arthroplasty that adapts treatment to an individual’s venous thromboembolism risk.Given that both minor and major surgery-related bleeding events following arthroplasty could lead to prosthetic joint infections (PJIs), the study includes PJI as a study outcome.The enrolment of a large number of patients from various teaching hospitals, general hospitals and private clinics across the Netherlands increases the generalisability of this study.The large sample size is both a recruitment challenge and a potential limitation of the feasibility of this study.

## Introduction

 Venous thromboembolism (VTE)^1^ primarily affects the deep veins of the leg (deep vein thrombosis (DVT)) and the pulmonary arteries (pulmonary embolism (PE)^2^). VTE is not only associated with considerable chronic morbidity leading to loss of quality of life but also with mortality. Patients undergoing elective total hip arthroplasty (THA) or total knee arthroplasty (TKA) have a high risk of postoperative VTE. Therefore, guidelines recommend prophylactic anticoagulant therapy after THA and TKA for all patients, although the type and length of treatment are under debate and differ between guidelines.^3^,^5^

Despite pharmacological thromboprophylaxis, 1.0%–1.5% of all patients still develop symptomatic VTE after THA/TKA.^6^ The main problem with the current ‘one-size-fits-all’ approach is that patients are considered to have an equal risk of thrombosis, while in reality, various individual and surgery-related factors influence VTE risk. For example, fast-track surgery protocols,^7^ which involve early mobilisation with subsequent reduction of hospital stay and opioid-sparing anaesthesia protocols, have greatly reduced VTE risk.^8^ Multiple studies have shown that in a large unselected population of patients undergoing THA/TKA, the incidence of VTE following fast-track surgery is <1.0% within 3 months, even when thromboprophylaxis was only administered during hospital admission (1–2 days).^8^,^11^ This implies that a large group of patients might currently be overtreated with thromboprophylactic therapy and are unnecessarily exposed to its burden and associated risk of bleeding. Major bleeding occurs in at least 0.5% of anticoagulated patients after THA/TKA, and minor bleeding, including clinically relevant non-major bleeding (CRNMB), occurs in about 6%.^12 13^ In addition to the general morbidity related to bleeding, a large surgery site-related haematoma increases the risk of an implant-associated infection and, therefore, the likelihood of revision surgery.^14^ Moreover, bleeding leads to prolonged wound drainage, which necessitates extended hospitalisation.^15^

At the other side of the spectrum, there must be patients with a high risk of VTE, as the average risk in the overall THA/TKA population is still 1.0%–1.5% despite thromboprophylaxis therapy.^6^ For instance, in patients with a history of VTE, the VTE risk following surgery is between 5% and 10%.^16^ For these patients, the current dose and duration of thromboprophylaxis might be insufficient, as they develop VTE despite prophylaxis.

Considering the above, important improvements can be expected from a tailored thromboprophylaxis strategy based on an individual’s risk profile. For patients with a low VTE risk, short-term thromboprophylaxis may be sufficient, while patients with a high VTE risk may benefit from an increased duration and higher, therapeutically dosed thromboprophylaxis. Hence, both thromboembolic and bleeding complications could be minimised, and a large proportion of patients will not need to be exposed to 4 weeks of anticoagulants, leading to societal cost savings.^17^

### Study objectives

The DISTINCT (inDividual, targeted thrombosIS prophylaxis versus the standard ‘one-size-fits-all’ approach in patients undergoing Total hIp or total kNee replaCemenT) trial aims to tailor thromboprophylaxis based on an individual’s estimated VTE risk. This VTE risk will be predicted by the recently developed and externally validated Thrombosis Risk Prediction following total hip and knee arthroplasty (TRiP(plasty)) score, specifically designed to predict an individual’s 90-day postoperative VTE risk after THA and TKA.^18^ We hypothesise that:

In patients with a low 90-day postoperative VTE risk (predicted risk <1.0%), thromboprophylaxis can be safely shortened to in-hospital duration only, without increasing the VTE risk, potentially reducing the incidence of CRNMB and minor bleeds.In patients with a high 90-day postoperative VTE risk (predicted risk >1.5%), high-dose thromboprophylaxis for 6 weeks is more effective in preventing symptomatic VTE compared with the standard prophylaxis. In addition, we expect that the benefits of this approach outweigh the potentially increased risk of bleeding.

Patients with an intermediate 90-day postoperative VTE risk (predicted risk ≥1.0% and ≤1.5%) receiving standard prophylaxis will be included to validate the predicted VTE risk. In addition, this group acts as a safety margin to ensure patient safety for the abovementioned interventions.

## Methods and analysis

### Summary of project status

Medical Research Ethics Committee approval was obtained in September 2024, with the first patient enrolled in November 2024. Recruitment is currently underway in nine hospitals in the Netherlands, with more than 850 patients enrolled to date. Final enrolment is planned for March 2027 in DISTINCT-1, March 2028 in DISTINCT-2 and July 2030 in DISTINCT-3.

### Study design

The DISTINCT trial is a national, multicentre, randomised, multiarm, open-label trial with blinded outcome adjudication. Patients will be recruited from teaching hospitals, general hospitals and private clinics across the Netherlands.

The study will consist of three study arms (figure 1) to which patients will be allocated based on their predicted VTE risk, as calculated by the TRiP(plasty) score (figure 2).^18^ Patients will either be assigned to the low VTE risk study arm: DISTINCT-1 trial (predicted 90-day postoperative VTE risk <1%), the intermediate VTE risk study arm: DISTINCT-2 study (predicted VTE risk ≥1% and ≤1.5%) or the high VTE risk study arm: DISTINCT-3 trial (predicted VTE risk >1.5%). Patients in the DISTINCT-1 trial will be randomised to either short-duration thromboprophylaxis (in-hospital only) or the control treatment (standard thromboprophylaxis). This study arm will be analysed as a non-inferiority trial. In the DISTINCT-2 study, participants will be treated with standard thromboprophylaxis. This study arm will be observational. Participants in the DISTINCT-3 trial will be randomised between the intervention (higher dose and longer duration thromboprophylaxis) and the control treatment (standard thromboprophylaxis). This study arm will be analysed as a superiority trial. All primary outcomes will be assessed up to 90 days following surgery. During the study, trial outcomes will be regularly evaluated by an independent Data and Safety Monitoring Board (DSMB). The Standard Protocol Items: Recommendations for Interventional Trials guidelines were followed when drafting the study protocol.^19 20^

**Figure 1 F1:**
[figure not shown]
Study design: DISTINCT (inDividual, targeted thrombosIS prophylaxis versus the standard ‘one-size-fits-all’ approach in patients undergoing Total hIp or total kNee replaCemenT) trial. TRiP(plasty) score, Thrombosis Risk Prediction following total hip and knee arthroplasty score; VTE, venous thromboembolism.

**Figure 2 F2:**
[figure not shown]
TRiP(plasty) model.^18^ The 90-day postoperative VTE risk can be calculated using the PI. The estimated individual postoperative VTE risk, as a percentage, can be calculated using the formula: exp(PI/(1+exp(PI))). BMI, body mass index; MI, myocardial infarction, PI, prognostic index; THA, total hip arthroplasty; TIA, transient ischaemic attack; TKA, total knee arthroplasty; TRiP(plasty) score, Thrombosis Risk Prediction following total hip and knee arthroplasty score; VTE, venous thromboembolism.

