### Patient screening and recruitment

Every patient who is scheduled to undergo THA/TKA at one of the participating centres will be screened by a trained study staff member. In case of eligibility, an individual’s postoperative VTE risk is predicted by the TRiP(plasty) score. Accordingly, patients will be assigned to either the DISTINCT-1, DISTINCT-2 or DISTINCT-3 studies and will receive telephonic and digital or written study information (online supplemental files 1-3). Patients willing to participate will provide digital or written informed consent.

Based on the validation study of the TRiP(plasty) score, the expected distribution of patients over DISTINCT-1, DISTINCT-2 and DISTINCT-3 is 55%, 30% and 15%, respectively.^18^ We aim to include a minimum of 10 participating centres, which collectively perform approximately 17 150 THA/TKA procedures annually, ensuring the feasibility of the study.

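### The Figure 2 caption misprints the formula for the risk that assigns patients to the three studies: it can exceed 1, and it lacks the factor of 100 that a percentage needs

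*Protocol article*

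**What the plan says.** The Figure 2 caption introduces the model with "The 90-day postoperative VTE risk can be calculated using the PI". It then says the individual risk, "as a percentage, can be calculated using the formula: exp(PI/(1+exp(PI", with three closing brackets after the quoted words. The division therefore sits inside the outer exponential, and the result is described as a percentage.

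The Study design section makes this the assignment rule: "patients will be allocated based on their predicted VTE risk, as calculated by the TRiP(plasty) score (figure 2". Its bands are below 1% for DISTINCT-1, 1% to 1.5% inclusive for DISTINCT-2, and above 1.5% for DISTINCT-3. Under Patient screening and recruitment, staff score each eligible patient and assign the study accordingly, and "the expected distribution of patients over DISTINCT-1, DISTINCT-2 and DISTINCT-3 is 55%, 30% and 15%, respectively". The article gives no other version of the formula and no worked example.

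**The concern.** The predicted risk decides whether a patient is randomised in the shortened-prophylaxis trial, observed, or randomised in the higher-dose trial. The intermediate band is only 0.5 percentage points wide, and the Study objectives describe that group as a safety margin between the two interventions. A small error in converting PI to risk is therefore large relative to the band.

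The printed expression looks like an inverse logit with one bracket out of place, and it has no factor of 100 to match the word percentage. Anyone who programs the score from the caption, or tries to reproduce the assignment from the publication, would get a different grouping from the one intended.

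**Working it through.** **Inputs.** Printed formula: Figure 2 caption. Cut-offs of 1.0% and 1.5%: Study design. Expected split of 55/30/15: Patient screening and recruitment. The article states no risk for any given PI, so there is no figure of its own to reproduce.

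**Definitions.** Printed: f = exp(PI/(1+exp(PI))). Inverse logit: p = exp(PI)/(1+exp(PI)), so PI = ln(p/(1−p)) and 1/(1+exp(PI)) = 1−p.

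**1. Is f a probability?** f = 1 at PI = 0 and 1.309 at PI = 1. It peaks at 1.321 near PI = 1.28, then falls to 1.153 at PI = 3. A risk can neither exceed 1 nor fall as the prognostic index rises. At the same points p is 0.5 at PI = 0, 0.731 at PI = 1 and 0.953 at PI = 3.

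**2. Direction of the error.** ln f = (1−p) × ln(p/(1−p)) = ln p + H(p), where H(p) = −p ln p − (1−p) ln(1−p). H(p) is positive for every p between 0 and 1, so f exceeds p at every PI.

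**3. Literal reading, with f taken as a percentage.** The maximum is about 1.32, so nobody exceeds 1.5. Every PI below 0 (logistic risk below 50%) gives a value below 1 and goes to DISTINCT-1. A patient with logistic risk 1% would score about 0.011. This cannot be squared with an expected 15% of patients in DISTINCT-3, or with its target of 4100.

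**4. Reading with ×100 added and the bracket error kept.** At p = 1%, PI = −4.5951 and 0.99 × (−4.5951) = −4.5492, so f = 1.058%. At p = 1.5%, PI = −4.1846 and 0.985 × (−4.1846) = −4.1218, so f = 1.621%.

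| Logistic risk | Printed form × 100 | Ratio |
|---|---|---|
| 0.75% | 0.784% | 1.045 |
| 1.00% | 1.058% | 1.058 |
| 1.30% | 1.393% | 1.072 |
| 1.50% | 1.621% | 1.081 |
| 2.50% | 2.810% | 1.124 |

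**5. Effective cut-offs on reading 4.** f = 1.0% at PI = −4.649, a logistic risk of 0.948%. f = 1.5% at PI = −4.259, a logistic risk of 1.394%. The inverse logit reaches the two cut-offs at PI = −4.595 and −4.185. Patients from 0.948% to just under 1.0% would go to DISTINCT-2 instead of DISTINCT-1. Patients above 1.394% and up to 1.5% would go to DISTINCT-3 instead of DISTINCT-2. The second strip is 0.106/0.5 = 21% of the width of the intermediate band.

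**6. Share of patients: illustration only.** The distribution of PI is not given. If PI were normal and fitted to 55/30/15 (mean −4.652, SD 0.451), 4.8% of all patients would move at the lower cut-off and 4.2% at the upper, giving a split of 50.2/30.6/19.2. If risks were uniform within bands, 2.9% to 5.7% would move at the lower cut-off (DISTINCT-1 risks starting at 0% to 0.5%) and 0.30 × 0.106/0.5 = 6.4% at the upper.

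**The case against.** The best defence is that this is a typographical slip with no operational effect. The caption belongs to a journal article published after enrolment had begun. The assignment rests on a cited, externally validated score, and nothing says that staff compute the risk from the caption. The figure's artwork, which was not available for this check, may carry the correct form. Literal use would leave DISTINCT-3 empty, which would be noticed at once. All of this stands as an argument against assuming that the trial runs on the printed formula. It does not rescue the caption, whose brackets balance and whose expression is still not a risk.

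Three stronger inferences are tempting, and the article does not support them.

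- A reader might infer that patients have already been put in the wrong study. No passage shows what the screening calculator computes.
- A reader might take 0.948% and 1.394% as the result of using the formula exactly as printed. They need a factor of 100 that the caption lacks; the strictly literal result is step 3 of the working.
- A reader might call this an error in the trial's eligibility threshold. The Eligibility criteria do not include the score, which is applied after eligibility to choose the study.

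It is also fair to say that assignment precedes randomisation and depends on baseline data alone. A shifted cut-off would change who is in each study, but it would not bias the 1:1 comparisons within DISTINCT-1 or DISTINCT-3. Finally, the article never calls the model logistic. That is inferred from the terms of the formula and should be checked against the source.

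**Conclusion.** The point holds as an error in the published assignment formula. That the expression is not a probability needs no outside source. That the inverse logit was intended is a strong inference from its terms. The missing factor of 100 is a second slip in the same sentence.

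The size depends on the reading. Taken literally as a percentage, the formula admits nobody to DISTINCT-3. With ×100 supplied and the bracket left as printed, it overstates risk by 5.8% in relative terms at 1.0% and 8.1% at 1.5%. The effective cut-offs drop by about 0.05 and 0.11 percentage points, and every shift is to the next higher-risk study. Both statements are conditional on the caption being used. Actual misassignment is not shown, and the shares in step 6 rest on assumed distributions.

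It still deserves correction, because the Study design section refers to this figure for the rule that places every patient and nothing elsewhere in the article corrects it.

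**What to change.** 1. Check the formula against the source model. If the model is logistic, as the terms imply, correct the caption to: risk (%) = 100 × exp(PI)/(1+exp(PI)).
2. Confirm that the calculator used at screening applies the verified form, for instance by entering PI = −4.595 and −4.185, which should return 1.0% and 1.5%.
3. Only if it does not, recompute the scores of the enrolled patients (more than 850 at publication), list those whose assigned study differs, and refer the list to the trial steering committee and the DSMB.

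Steps 1 and 2 cost a one-line correction and a short check. Step 3 arises only if the check fails; it needs no new data as long as the score inputs were recorded. No cut-off, treatment or sample size changes.

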### Eligibility criteria

Patients are eligible for the study if they undergo elective primary THA or TKA in one of the participating centres and meet the criteria listed below.

Inclusion criteria:

Elective THA or TKA.Aged 18 years or older.

Exclusion criteria:

Primary arthroplasty for fractures.Revision surgery.Hemiarthroplasty.Pregnancy.Current use of therapeutic anticoagulant therapy of any type (eg, Low-Molecular-Weight Heparin (LMWH), Direct Oral Anticoagulant (DOAC) or vitamin K antagonist).A contraindication for either study drug/treatment.Insufficient knowledge of the Dutch language.Insufficient mental or physical ability to fulfil trial requirements.Active malignancy (ie, cancer diagnosis or anti-cancer treatment within 6 months before surgery, excluding basal-cell or squamous-cell carcinoma of the skin).Patients using platelet aggregation inhibitors that cannot be temporarily discontinued at the discretion of their treating physician.

### Patient screening and recruitment

Every patient who is scheduled to undergo THA/TKA at one of the participating centres will be screened by a trained study staff member. In case of eligibility, an individual’s postoperative VTE risk is predicted by the TRiP(plasty) score. Accordingly, patients will be assigned to either the DISTINCT-1, DISTINCT-2 or DISTINCT-3 studies and will receive telephonic and digital or written study information (online supplemental files 1-3). Patients willing to participate will provide digital or written informed consent.

Based on the validation study of the TRiP(plasty) score, the expected distribution of patients over DISTINCT-1, DISTINCT-2 and DISTINCT-3 is 55%, 30% and 15%, respectively.^18^ We aim to include a minimum of 10 participating centres, which collectively perform approximately 17 150 THA/TKA procedures annually, ensuring the feasibility of the study.

### Randomisation, blinding and treatment allocation

Approximately 2 weeks before surgery, patients will be randomised centrally by a clinical data management system (Castor Electronic Data Capture (EDC), V.2025.2.4.0 Amsterdam, the Netherlands). Randomisation within the DISTINCT-1 and DISTINCT-3 trials will be performed in a 1:1 ratio, using block randomisation with variable block sizes and stratified by study centre. This is an open-label study, meaning that patients and treating physicians will not be blinded to the intervention; however, outcome assessors will be. The DISTINCT-2 study is an observational study arm.

### Study interventions

For the DISTINCT-1 trial, patients will be randomised between:

InterventionIn-hospital thromboprophylaxis only: any type of LMWH or DOAC in a prophylactic dose, as approved by the Dutch antithrombotic guidelines, administered until hospital discharge.^21^ The first dose of LMWH should be administered within 6–24 hours following surgery; the first dose of apixaban within 12–24 hours; the first dose of rivaroxaban within 6–10 hours and the first dose of dabigatran within 1–4 hours. The type of anticoagulant administered according to the local protocol (the same as that used in the control group). Patients undergoing outpatient THA or TKA (surgery and discharge on the same day) will receive one dose of thromboprophylaxis.ControlStandard thromboprophylaxis for 4 weeks: any type of LMWH or DOAC in a prophylactic dose, as approved by the Dutch guidelines.^21^ The first dose of LMWH should be administered within 6–24 hours following surgery; the first dose of apixaban within 12–24 hours; the first dose of rivaroxaban within 6–10 hours and the first dose of dabigatran within 1–4 hours. The type of anticoagulant administered is according to the local protocol.

DISTINCT-2 study

Standard thromboprophylaxis for 4 weeks: any type of LMWH or DOAC in a prophylactic dose, as approved by the Dutch guidelines.^21^ The first dose of LMWH should be administered within 6–24 hours following surgery; the first dose of apixaban within 12–24 hours; the first dose of rivaroxaban within 6–10 hours and the first dose of dabigatran within 1–4 hours. The type of anticoagulant administered is according to the local protocol.

For the DISTINCT-3 trial, patients will be randomised between:

InterventionDays 0–2: any type of LMWH or DOAC in a prophylactic dose, as approved by the Dutch guidelines.^21^ The first dose of LMWH should be administered within 6–24 hours following surgery; the first dose of apixaban within 12–24 hours; the first dose of rivaroxaban within 6–10 hours and the first dose of dabigatran within 1–4 hours following surgery. The type of anticoagulant administered is according to the local protocol.Day 3: apixaban, 5 mg, two times per day, continued until 6 weeks after surgery. The start of the therapy is conditional on the fact that no active bleeding of the surgical wound can be observed. In the case of active bleeding, the prophylactic dose of thrombosis prophylaxis is continued. Thereafter, when no active bleeding has been observed for 24 hours following the bleeding, the 5 mg, two times per day, apixaban treatment will be initiated (off note, the total duration of thromboprophylaxis will not be extended and is maximised up to 6 weeks following surgery).

The timing of the first dose of apixaban is dependent on the type of preceding thromboprophylaxis during days 0–2: the first dose of study medication (apixaban) must be administered within 12–24 hours following the last dose of the initial provided thromboprophylaxis. The 5 mg, two times per day, apixaban dose will be adjusted to 2.5 mg, two times per day, in case of impaired kidney function (defined as estimated Glomerular Filtration Rate (eGFR) 15–30 mL/min). The use of any platelet aggregation inhibitors should be discontinued 5 days prior to surgery until 6 weeks postoperative.

ControlStandard thromboprophylaxis for 4 weeks: any type of LMWH or DOAC in a prophylactic dose, as approved by the Dutch guidelines.^21^ The first dose of LMWH should be administered within 6–24 hours following surgery; the first dose of apixaban within 12–24 hours; the first dose of rivaroxaban within 6–10 hours and the first dose of dabigatran within 1–4 hours. Thromboprophylaxis is continued until 4 weeks after surgery. The applied type of anticoagulant is according to the local protocol.

